## 2. Efficacy evaluation index

### (1) Primary efficacy measures

- **【Oral clinical testing indicators】** During the screening period, before administration, and follow-up period, D90±3, D180±5, and D360±5 were examined with Florida probe, and the measured value of D90±3 was used as the evaluation endpoint.  
Periodontal attachment level AL (PD+GR).

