### (2) Secondary efficacy measures

- **【Radiological detection index】** D90±3, D180±5, D360±5 were examined during the screening period and follow-up period, and the indicators in the screening period were used as the baseline index, and the measured value of D180±5 was used as the evaluation endpoint.
- Change in periodontal defect height at 3 months, 6 months, and 12 months after the end of treatment compared to baseline (CBCT measurements, change in periodontal defect height = difference in distance from enamel bone boundary to alveolar crest).
- Change in mean density of alveolar ridge after 3 months, 6 months, 12 months after the end of treatment compared to baseline (CBCT measurement results).

[Oral clinical testing indicators]: During the screening period, pre-administration, and follow-up periods, D90±3, D180±5, and D360±5 were examined with Florida probes, and the measured values of D90±3 were used as the evaluation endpoints.

- Periodontal probing depth PD compared to baseline
- Periodontal healing compared to baseline (probing bleeding index BOP, gingival recession GR, tooth looseness TM).

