### **4. Anticipated adverse events and treatment plans**

Anticipated Adverse Events: Adverse events that subjects may face while participating in the study. Possible

adverse events in this study and The handling measures are as follows.

(1) Local adverse events on teeth: mild inflammatory reactions such as mild redness and swelling of the gums; severe inflammatory reactions such as loose periodontal pockets and pus overflow, periodontal ligament edema, etc. The researchers conducted symptomatic treatment in accordance with the routine clinical diagnosis and treatment of periodontal disease: for mild inflammatory reactions in periodontal tissue, local irrigation of the periodontal pockets and gargling with mouthwash were performed; for severe inflammatory reactions in periodontal tissues, debridement of the periodontal pockets was performed. Antibiotics are built into the bag. If necessary, local abscesses can be incised and drained and gargled with mouthwash.

(2) Injection local hematoma: It manifests as injection local blood vessel damage, intra-tissue bleeding, and purple-red petechial or masses under the mucosa or subcutaneously. Principles of prevention and treatment: If hematoma has appeared locally, immediate compression can be used to stop the bleeding and cold compress should be applied; subjects are instructed to apply hot compress after 48 hours to promote the absorption and dissipation of the hematoma. Antibiotics and hemostatic drugs may be given as appropriate.

(3) Systemic adverse events: chills, fever, mild headache, which can subside naturally.

(4) Progression of periodontitis: During the study period, if the subject's periodontitis progresses, the researcher will judge whether to intervene or not. For example, other treatments or drugs may be used to intervene that may affect the study, or the researcher may evaluate whether to withdraw.

(5) In clinical drug research, a very small number of subjects may suffer from shock due to allergic reactions. Once a subject develops anaphylactic shock, treatment will be carried out in accordance with the "Anaphylactic Shock First Aid Plan Standard Operations".

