#### **(1) Analyzed Population:**

Statistical analysis datasets for the study results included the full analysis dataset (FAS), the protocol compliance dataset (PPS), and the safety Sexuality dataset (SS).

**Full Analysis Set (FAS):** for all cases that had used the study drug after enrollment and had completed at least one efficacy assessment. cases with at least one efficacy assessment completed after enrollment. The estimation of missing values for the main indicators was performed by the method of LOCF (last observation carrying forward).

**Per Protocol Set (PPS):** a subset of the FAS, all cases that comply with the study protocol,

have good compliance, do not use prohibited drugs during the study period, have completed 6 months of clinical observation, and have completed the CRF;

**Safety Set (SS):** all cases that received the study drug after enrollment and had at least one safety assessment. Cases.

In this study, baseline information was analyzed using FAS and PPS analysis. Primary efficacy indicators, secondary efficacy indicators, etc. were analyzed by both FAS and PPS. However, the conclusions obtained from FAS analysis were the main conclusions. When the conclusions from FAS and PPS are consistent, the credibility of the conclusions can be increased.

In the safety analysis, adverse events and adverse reactions, vital signs, and laboratory indicators were analyzed using SS. subjects who were terminated prematurely due to adverse events and various non-therapeutic reasons were included in the safety analysis.

**(2) Statistical analysis plan:** the analysis of the study results included the description of the distribution of subjects, the balance analysis of baseline indicators, the analysis of efficacy, and the analysis of safety.

Mean, standard deviation, median, quartile, minimum and maximum values were used for the statistical description of the measurement data. Comparisons between groups were performed by ANOVA or Kruskal-Wallis rank sum test, and comparisons in groups were performed by paired t-test or Wilcoxon signed rank test. test for within-group comparisons.

Statistical descriptions of counts and rank data used rate or composition ratio, comparisons of count data used  $\chi^2$  test or Fisher's exact probability method, and comparisons of rank data used Kruskal-Wallis rank-sum test.

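### One per-protocol set with a 6-month follow-up condition serves endpoints read at D90, so the supportive per-protocol analysis of the primary endpoint depends on events after that endpoint

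*Protocol*

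**What the plan says.** Protocol section (XIX) 2.(1), Analyzed Population, defines one PPS as a subset of the FAS. Its conditions apply jointly: compliance with the protocol, good compliance, "do not use prohibited drugs during the study period", "have completed 6 months of clinical observation", and a completed CRF. The same section applies the two sets to all efficacy data: "Primary efficacy indicators, secondary efficacy indicators, etc. were analyzed by both FAS and PPS". It ranks them: "However, the conclusions obtained from FAS analysis were the main conclusions". It also gives the PPS a confirming role: "When the conclusions from FAS and PPS are consistent, the credibility of the conclusions can be increased".

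Section (15) 2.(1) fixes the time of the primary endpoint, AL: "the measured value of D90±3 was used as the evaluation endpoint". Section (15) 2.(2) uses D90 in the same way for the secondary probing measures (PD, BOP, GR, TM). Only the CBCT measures are later: "the measured value of D180±5 was used as the evaluation endpoint". The efficacy part of the scenario summary gives the same times. No section defines a separate PPS for the D90 endpoints.

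**The concern.** A per-protocol analysis of a D90 endpoint is meant to show the treatment difference among subjects who kept to the protocol up to D90. Here membership also depends on what happens afterwards. A subject who is fully compliant through D90, has a valid AL reading and leaves at D120 is removed. So is one who takes a prohibited drug at month 8.

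If such events were unrelated to outcome and arm, the only cost would be precision. The protocol gives reason to doubt that they are unrelated. Section (16) 4, item (4), says that on progression of periodontitis other treatments or drugs may be used, or "the researcher may evaluate whether to withdraw". Section (7) 3 makes poor follow-up compliance and the use of certain drugs grounds for exit. Section (V) 3 states that subjects and injecting investigators cannot be blinded, so departure may differ by arm.

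What is at stake is the credibility check. Agreement or disagreement between FAS and PPS at D90 could then come from attrition after the endpoint and say nothing about compliance before it.

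**Working it through.** **Set against endpoint.** The protocol states no figure to reproduce here. The defect shows when the times are put side by side.

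| Measure | Evaluated at | 6-month condition reaches | Drug condition reaches |
|---|---|---|---|
| AL (primary) | D90 | D180, 90 days later | D360, 270 days later |
| PD, BOP, GR, TM | D90 | D180, 90 days later | D360, 270 days later |
| CBCT measures | D180 | D180, matches | D360, 180 days later |

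The D360 limit follows from the 12-month follow-up in section (XX). The FAS needs only study treatment and one efficacy assessment, so a subject with a D90 reading stays in it whatever happens later.

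**Inputs for the size.** From section (8): 33 saline, 33 single-injection and 30 double-injection subjects, total 96; α = 0.05, with 1−α/2 in the formula; power 0.80. The protocol does not give δ, S, the loss between D90 and D180, or how that loss depends on outcome or arm. All values of these below are assumptions.

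**Precision, at an assumed loss p of 5% to 15%.**
- D90 values removed: 96 × 0.05 = 4.8, about 5; 96 × 0.15 = 14.4, about 14.
- Widening of the standard error: 1/√(1−p) − 1 = 2.6% at p = 0.05 and 8.5% at p = 0.15.
- Scale: 33 per arm detect (1.960 + 0.842) × √(2/33) = 0.69 SD with 80% power. This is solved back from the arm size and is not a planned effect. At that effect, power in the PPS falls from 80.0% to 78.0% (5% loss) and 73.3% (15% loss). For 33 against 30 it falls from 78.1% to 76.0% and 71.3%.

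**Shift, at an assumed loss of 15% in saline and 5% in a cell arm.** Let leavers be d SD worse at D90 than stayers in their own arm. The whole-arm mean is a mixture, so removing leavers makes the arm look better by p × d.
- Saline: 0.15d. Cell: 0.05d. Change in the difference: (0.15 − 0.05)d = 0.10d.
- d = 0.5 gives 0.05 SD; d = 1 gives 0.10 SD.
- Direction: saline gains more from the removal, so an advantage of cells shrinks towards no difference.
- If d is instead measured from the whole-arm mean, the gain is p × d/(1−p). The shift is then (0.15/0.85 − 0.05/0.95)d = 0.124d, or 0.06 to 0.12 SD.

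**Sensitivity, with loss in one arm only.** If the odds of leaving double per SD of worse outcome, the shift is 0.03, 0.07 and 0.13 SD at 5%, 10% and 20% loss. If exactly the worst outcomes leave, an extreme case, it is 0.11, 0.19 and 0.35 SD.

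**The case against.** The strongest reply is that the FAS leads. A reader might infer that the primary result loses valid data. It does not: every observed D90 value stays in the analysis that carries the main conclusions, and only the supportive analysis is touched. This stands and limits the weight of the point.

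Six months also has a visible rationale. The visit schedule groups D7 to D180 as the research follow-up period, separate from long-term follow-up at D360, and D180 is the evaluation time for imaging. One set keeps all analyses on the same subjects. That justifies the condition for the CBCT measures but not for the probing measures.

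Section (XIX) 1 provides for a joint review before database lock that settles the analysed population. The definition could be refined there, but nothing says that it will be, and amending the written rule beforehand is cleaner than judgement once data are in hand.

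The support for outcome-related loss is indirect. Section (16) 4 allows withdrawal on progression at any time. It does not show that such exits fall after D90. Distortion is therefore possible, not demonstrated.

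A reader might also infer that the 6-month rule is too loose for D360, because it admits subjects without a 12-month reading. The documents do not support that. No measure has D360 as its evaluation endpoint, and the joint conditions on protocol compliance and CRF completion may already exclude such subjects.

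**Conclusion.** The mismatch is on the face of the protocol: one PPS, defined by conditions running to D180 or beyond, is applied to endpoints evaluated at D90. It should be corrected, but it is a minor to moderate defect in a supportive analysis. The main FAS conclusion is unaffected.

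The size cannot be known from the protocol. Under the assumed 5-15% loss, precision suffers modestly. Under the assumed 15% against 5% loss with leavers 0.5-1 SD worse than stayers, the shift of about 0.05-0.10 SD is small beside the roughly 0.69 SD that 33 per arm can detect. A reader might infer that the rule would falsely confirm a benefit. In this scenario it works the other way, and the direction would reverse only if the pattern of loss did.

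**What to change.** Reword the PPS definition in section (XIX) 2.(1) so that membership is endpoint-specific.

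- **D90 probing endpoints (AL, PD, BOP, GR, TM):** require protocol compliance and no prohibited drugs up to the D90 visit, and an available D90 assessment. Drop the 6-month and completed-CRF conditions for these endpoints.
- **D180 imaging endpoints:** keep the 6-month requirement, with compliance and the drug condition assessed through the D180 visit.

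Do not turn D90±3 into a new exclusion rule. Section (XX) foresees visits outside the window and recalculates the next one, so a strict window could itself discard usable D90 readings.

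The cost is one reworded definition and a membership flag per endpoint time. No data collection, visit or sample size changes.

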## **(XX) Follow up plan and implementation methods**

The follow-up period of this study was 12 months, with telephone follow-up at  $D7 \pm 1$  after local injection treatment and regular follow-up at  $D30 \pm 3$ ,  $D90 \pm 3$ ,  $D180 \pm 5$ , and  $D360 \pm 5$ . The investigator should observe the subjects strictly according to the protocol, and the subjects should try to follow up regularly as requested by the investigator. During the study period, treatment and follow-up should be performed in strict accordance with the protocol, taking into account the fact that a time window of  $\pm 3$  days is allowed from 1 month after treatment with the stem cell preparation, and a time window of  $\pm 5$  days is allowed from 6 months after treatment. If a subject exceeds the window at a follow-up visit, the next follow-up visit should be recalculated based on the time of the previous visit.

The examinations required to be performed at each follow-up visit were conducted by the investigator, and the relevant examinations were conducted in the imaging department, laboratory department and other specialized departments of the research center, and timely, accurate and complete records were made of the clinical indicators, laboratory results and imaging results of each observation, and of the combination of medications, adverse events, and so on. For subjects with adverse reactions, all indicators of the screening period were followed up until they were normalized.

**1. Post-treatment follow-up 1:** Telephone follow-up 1 week ( $D7 \pm 1$  day) after the end of treatment.

- a. Record of adverse events
- b. Record of co-administration of drugs/treatment

**2. Post-treatment follow-up 2:** 1 month ( $D30 \pm 3$  days) after the end of treatment.

a. Vital signs: respiration, heart rate, blood pressure (systolic, diastolic), temperature (axillary), clinical assessment of the general body condition, and another checkup  $2h \pm 30min$  after the end of the second administration of treatment for the subjects in the secondary stem cell administration group in the second phase of this study.

b. Laboratory tests:

- Blood count: leukocytes, erythrocytes, hemoglobin, erythrocyte pressure volume, mean erythrocyte volume, mean hemoglobin concentration, platelet count, mean platelet volume, platelet pressure, neutrophil, lymphocytes, monocytes, eosinophils, basophils, absolute value of neutrophils, absolute value of lymphocytes, absolute value of monocytes, absolute value of eosinophils, absolute value of basophils, erythrocyte distribution width SD, erythrocyte distribution width CV, large platelet ratio, platelet distribution width.
- Liver and kidney function: alanine aminotransferase, aspartate aminotransferase, total protein, albumin, globulin, white globule ratio, total bilirubin, direct bilirubin, indirect bilirubin, alkaline phosphatase, creatinine, gamma-glutamyltransferase, lactate dehydrogenase, creatine kinase, urea enzyme, lactate dehydrogenase, creatine kinase, urea, uric acid, total carbon dioxide, glucose.
- Infectious disease detection: HBsAg, HBsAb, HBeAg, HBeAb, HBcAb, Anti-HCV, HIVcombin, Anti-TP, CMV-IgM, CMV-IgG.
- Immunological tests: IgA, IgG, IgM, Toal IgE.
- Pregnancy test: blood beta-HCG, for premenopausal female subjects only.
- Inflammatory indicators: only for subjects in the secondary stem cell dosing group in phase II of this study before secondary dosing treatment, examined  $2h \pm 30min$  after the end of treatment.

c. Record of adverse events

d. Record of combined medications/treatments

e. Intraoral photography: photographic record of oral cavity and treatment site conditions.

**3. Post-treatment follow-up 3:** conducted 3 months ( $D90 \pm 3$  days) after the end of treatment.

a. Periodontal Clinical Indicators: Periodontal Clinical Indicators: Periodontal examinations were standardized using the Florida Probe of the Beijing Stomatological Hospital of Capital Medical University. Records: periodontal attachment level AL, periodontal probing depth PD, probing bleeding index BOP, gingival recession GR, and tooth looseness TM.

b. Laboratory tests:

- Blood count: leukocytes, erythrocytes, hemoglobin, erythrocyte pressure volume, mean erythrocyte volume, mean hemoglobin concentration, platelet count, mean platelet volume, platelet pressure, neutrophil, Lymphocytes, monocytes, eosinophils, basophils, absolute value of neutrophils, absolute value of lymphocytes, absolute value of monocytes, absolute value of eosinophils, absolute value of basophils, erythrocyte distribution width SD, erythrocyte distribution width CV, large platelet ratio, platelet distribution width.
- Hepatic and renal function: alanine aminotransferase, aspartate aminotransferase, total protein, albumin, globulin, leukoglobulin ratio, total bilirubin, direct bilirubin, indirect bilirubin, alkaline phosphatase, creatinine, gamma-glutamyltransferase enzyme, lactate

dehydrogenase, creatine kinase, urea, uric acid, total carbon dioxide, glucose.

- Infectious disease tests: HBsAg, HBsAb, HBeAg, HBeAb, HBcAb, Anti-HCV, HIVcombin, Anti-TP, CMV-IgM, CMV-IgG.
- Immunologic tests: IgA, IgG, IgM, total IgE.
- Pregnancy test: blood beta-HCG for premenopausal female subjects only.
- c. Record of adverse events
- d. Record of co-medication/treatment
- e. Imaging: CBCT examination.
- f. Intraoral photography: photographic record of oral cavity and treatment site conditions.

**4. Post-treatment follow-up 4:** conducted 6 months ( $D180 \pm 5$  days) after the end of treatment.

a. Periodontal clinical indicators: The periodontal examination was standardized using the Florida Probe of the Beijing Stomatological Hospital of Capital Medical University. Examination. Records: periodontal attachment level AL, periodontal probing depth PD, probing bleeding index BOP, gingival recession GR, tooth looseness TM. recession GR, and tooth looseness TM.

b. Laboratory tests:

- Blood count: leukocytes, erythrocytes, hemoglobin, red blood cell pressure, mean red blood cell volume, mean hemoglobin concentration, platelet count, mean platelet volume, platelet pressure volume, neutrophils, lymphocytes, monocytes, eosinophils, basophils, absolute value of neutrophils, absolute value of lymphocytes, absolute value of monocytes, absolute value of eosinophils, absolute value of basophils, erythrocyte distribution width SD, erythrocyte distribution width CV, large platelet ratio, platelet distribution width.
- Liver and kidney function: alanine aminotransferase, aspartate aminotransferase, total protein, albumin, globulin, white globule ratio, total bilirubin, direct bilirubin, indirect bilirubin, alkaline phosphatase, creatinine, gamma-glutamyltransferase enzyme, lactate dehydrogenase, creatine kinase, urea, uric acid, total carbon dioxide, glucose.
- Infectious disease tests: HBsAg, HBsAb, HBeAg, HBeAb, HBcAb, Anti-HCV, HIVcombin, Anti-TP, CMV-IgM, CMV-IgG.
- Immunologic tests: IgA, IgG, IgM, total IgE.
- Pregnancy test: blood beta-HCG for premenopausal female subjects only.

- c. Record of adverse events
- d. Record of co-medication/treatment
- e. Imaging: CBCT examination.
- f. Intraoral photography: photographic documentation of the oral cavity and treatment site conditions.

**5. Long-term follow-up:** 12 months ( $D360 \pm 5$  days) after the end of treatment.

a. Periodontal clinical indicators: The periodontal examination was standardized using the Florida Probe of the Beijing Stomatological Hospital of Capital Medical University. Records: periodontal attachment level AL, periodontal probing depth PD, probing bleeding index BOP, gingival recession GR, tooth looseness TM.

b. Laboratory tests:

- Immunologic tests: IgA, IgG, IgM, total IgE.

c. Record of adverse events

- d. Record of co-medication/treatment
- e. Imaging: CBCT examination.
- f. Intraoral photography: photographic record of oral cavity and treatment site conditions.

